## Phase 2: Clinical epidemiology

The design of this clinical epidemiological phase of the study will comprise an ambispective analysis, involving first, a retrospective cohort of all patients with COVID-19 followed in one of the dedicated COVID-19 centers in the cities of Ouagadougou or Bobo-Dioulasso since the beginning of the epidemic; and second, prospective inclusion of all patients who present up until the end of the epidemic, or at the latest, 6 months after the start of the study. Retrospective data will be collected after study initiation, from the medical files of patients diagnosed since the start of the epidemic but before the study was initiated. These data will be used (if possible, depending on the number of cases collected) to construct a score to predict the occurrence of severe complications and death related to COVID-19, which could then be used to optimize patient management. The score will be validated in the prospective cohort to be included after study initiation.

### Participant characteristics

The eligible population for this phase of the study will comprise all patients with a positive diagnosis of COVID-19 and followed in either of the two participating cities (Ouagadougou and Bobo-Dioulasso). In Burkina Faso, the epidemic is principally active in these two cities, the largest in the country, and the dedicated COVID-19 centers in these two cities manage almost all patients with a positive diagnosis since the start of the epidemic. The four main management sites are follows:In Ouagadougou: University hospital Yalgado, University hospital Bogodogo and University hospital Tengandogo;In Bobo Dioulasso: University hospital Sourou-Sanou.

### Inclusion criteria

All patients followed for COVID-19 (whether they are or were hospitalized or not), in the reference management centers cited above, or in outpatient care, in Ouagadougou and Bobo-Dioulasso.

### Non-inclusion criteria

Patients who refuse the use of their medical records for research purposes.

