### Study endpoints

This phase of the study will have two primary endpoints, namely:The proportion of severe complications (defined as severe pneumonia, acute respiratory distress syndrome, sepsis or septic shock) in patients infected with SARS-CoV-2;The proportion of deaths in patients infected with SARS-CoV-2.

Secondary endpoints will be as follows:The proportion of severe complications according to age group and gender;The proportion of deaths according to age group and gender;

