### Sample size calculation

No sample size can be calculated for this phase of the study. Exhaustive inclusion of all cases of COVID-19 followed in the cities of Ouagadougou and Bobo-Dioulasso is planned. At least 1,000 cases are anticipated (as of 28 November 2020, Burkina Faso had a total of 2,886 confirmed cases of COVID-19, of whom 984 were women and 1902 were men). The statistical power of the analyses will be calculated a posteriori*.*

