## Discussion

### Communication and mobilization of the community

Given the nature of this study, and before the start of the sero-epidemiological (phase 1) and socio-anthropological (phase 3) components, we will openly dialogue with community leaders in the study zones. Through information to these leaders, to raise awareness about the positive repercussions of the study, we hope to ensure they will advocate for the study and convince the members of their communities to participate. Radio and/or television ads as well as public announcers with megaphones will also provide information to the public in the days prior to the researchers’ presence to collect data in the study zones. This widespread mobilization of the local community is key to achieving the inclusion and adherence necessary to guarantee the success of the study. In the general population, given that the blood draws will be performed in the participants’ homes, we plan to provide a small snack after the blood draw, comprised of a cold drink made of local fruit juices, and dry biscuits; these will be easy to handle without increasing the risk of contamination with SARS-CoV-2.

Participants in phase 2 (clinical epidemiology) who are hospitalized at the time of the study will receive written and oral information (patient information leaflet) about the study from a study investigator (physician). The information leaflet will outline the main objectives and procedures of the study and the expected risks and benefits. For participants who have difficulty understanding French, the written information will be complemented by oral information provided in the local language in the presence of a surrogate designated by the patient. For deceased patients, a request for exemption from the obligation to provide information will be submitted to the national ethics committee of Burkina Faso. The healthcare staff will try to contact as many recovered patients as possible to recover any data not available in the medical files, to ensure completeness of the CRFs, and minimize missing data. Recovered patients who accept to participate may come to the COVID-19 management center if they so desire to provide any data that is not available in the medical files. Their travel costs will be reimbursed in such cases.

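### Phase 2 death proportion: if the requested exemption for deceased patients is granted, refusal of record use can remove discharged survivors from the retrospective cohort but not earlier deaths

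*Protocol article*

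**What the plan says.** Phase 2 is ambispective. For the retrospective part, "Retrospective data will be collected after study initiation, from the medical files of patients diagnosed since the start of the epidemic" but before the study began. The prospective part takes patients who present afterwards. The sample size section states the intended coverage: "Exhaustive inclusion of all cases of COVID-19 followed in the cities of Ouagadougou and Bobo-Dioulasso is planned".

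The single non-inclusion criterion is "Patients who refuse the use of their medical records for research purposes". One of the two primary endpoints is "The proportion of deaths in patients infected with SARS-CoV-2".

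The Discussion, under communication and mobilization of the community, treats three groups differently:
- Patients "who are hospitalized at the time of the study will receive written and oral information (patient information leaflet) about the study".
- "For deceased patients, a request for exemption from the obligation to provide information will be submitted to the national ethics committee".
- For those who recovered, "The healthcare staff will try to contact as many recovered patients as possible to recover any data not available in the medical files", and participation in that step is voluntary.

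The Phase 2 statistical analysis section plans imputation and sensitivity analyses for missing data. It says nothing specific about patients who refuse.

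**The concern.** In the retrospective part, many outcomes are already fixed when refusal first becomes possible. A patient who died before study start cannot refuse, and the text describes no refusal by relatives. A patient discharged alive can refuse, and the non-inclusion criterion then removes that patient. With the exemption in place, exclusion therefore depends on the outcome that the primary endpoint measures: the numerator is kept whole and the denominator loses survivors.

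The planned missing-data methods do not repair this. A patient who is not included is outside the dataset, so there is no record to impute. Unlike sampling error, the shift does not shrink as more cases are collected.

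**Working it through.** The plan has no figure of its own to reproduce. It states that no sample size can be calculated for Phase 2, and it gives neither a refusal rate nor an expected death proportion.

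**Input from the protocol.** N = 1,000, from "At least 1,000 cases are anticipated" in the Phase 2 sample size section. This is an expectation, not a calculated target.

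**Assumptions, not in the documents.** True death proportion p = 5% or 10%, the same in both parts of the cohort. Refusal rate r among discharged retrospective survivors = 5%, 10% or 20%. Retrospective share f = one half. Refusals in the prospective part are set to zero, to isolate the mechanism. The exemption is granted and all deaths are retained.

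**Formula.** Observed pooled proportion = p / [p + (1 − p)(1 − f·r)].

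**Central case, r = 10%, so f·r = 0.05:**
- p = 5%: 0.05 / (0.05 + 0.95 × 0.95) = 0.05 / 0.9525 = 5.25%, a shift of 0.25 points.
- p = 10%: 0.10 / (0.10 + 0.90 × 0.95) = 0.10 / 0.955 = 10.47%, a shift of 0.47 points.

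**Range over r, with f = one half:**

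| r | f·r | true 5% reads | true 10% reads |
|---|---|---|---|
| 0% | 0 | 5.00% | 10.00% |
| 5% | 0.025 | 5.12% | 10.23% |
| 10% | 0.05 | 5.25% | 10.47% |
| 20% | 0.10 | 5.53% | 10.99% |

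**Retrospective cohort on its own (f = 1), r = 10%.** 5% reads 5.53% and 10% reads 10.99%.

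**Comparison with sampling error at N = 1,000.** Half-width = 1.96 × √[p(1 − p)/1,000], which is 1.35 points at p = 5% and 1.86 points at p = 10%. In the central case the shift is 0.25/1.35 = 18% and 0.47/1.86 = 25% of the half-width. Even if the whole cohort were retrospective, refusal would have to reach about 22% (p = 5%) or 17% (p = 10%) for the shift to equal the half-width.

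**If the exemption is not granted.** Deaths may be lost as well, and the sign can reverse. With f = 1, p = 5%, 5% of survivors refusing and 10% of deaths lost: 0.045 / (0.045 + 0.95 × 0.95) = 0.045 / 0.9475 = 4.75%.

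**Check of the correction.** Take 500 retrospective patients, p = 10%, r = 10%: 50 deaths, 450 survivors, 45 refusers. Uncorrected: 50/455 = 10.99%. With the discharged refusers added back: 50/(455 + 45) = 10.0%, the true value. Only the count of refusers is needed.

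**The case against.** The strongest reply is that excluding people who refuse is an ethical requirement, and that counting refusals is a detail that an article may leave to the full protocol. Both points stand. The absence of a refusal count is not the fault raised here. The point is that rules the article does state, taken together, make exclusion depend on survival.

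Four stronger readings are tempting, and the documents do not support them.

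- **That the bias is certain and always upward.** The exemption is only to be requested; nothing shows that it was granted. The bias also needs at least one refusal, and it can reverse if deaths are lost.
- **That survivors who cannot be reached also drop out.** Contact with recovered patients serves to complete missing data and is not stated as a condition of inclusion. Only active refusers leave.
- **That every retrospective refuser is a survivor.** A patient diagnosed before study start may still be in hospital, be informed there, refuse and die later. The argument is safe only for patients already discharged when they refuse.
- **That the prediction score is damaged.** The statistical analysis section describes a score for severe complications, judged by discrimination, sensitivity, specificity and predictive values. Survivors may themselves have had severe complications, so the loss of survivors does not carry over simply to that outcome. If refusal is unrelated to the predictors, it moves the intercept of a model for death but not its odds ratios.

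A reader might also set the shift against the precision at 2,886 cases. That is the national count of confirmed cases, not the planned cohort.

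**Conclusion.** The point holds conditionally. If the exemption is granted and any discharged retrospective survivor refuses record use, the primary death proportion is overstated. The direction then follows from the stated rules, but the size does not, because the refusal rate, the death proportion and the retrospective share are all assumed. In the central case the pooled figure moves from 5% to about 5.25%, or from 10% to about 10.5%, which is roughly a fifth to a quarter of the 95% half-width at 1,000 cases. This is a modest bias in a primary endpoint and no reason to doubt the design. It is worth acting on because the correction is nearly free and the count may not be recoverable once contacts have been made.

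**What to change.** Keep the exclusion of refusers' records, and add the following.

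1. Before contact with patients starts, have each centre count refusals by period (retrospective or prospective) and by whether the patient had already been discharged when refusing.
2. For the retrospective cohort, also report deaths / (included patients + already-discharged refusers). The protocol ends survival follow-up of recovered patients at discharge, so these refusers count as survivors by its own convention. Use this figure only if the exemption is granted and all deaths are retained; otherwise it would add a downward bias.
3. For patients still in care when they refuse, in either period, report the refusal count and show the death proportion over the range from no refuser dying to all refusers dying.
4. For severe complications, apply the same full range to all refusers, because a discharged refuser may have had one. A narrower range that stops at the observed rate would omit the case in which refusers fare worse.

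The cost is one count per centre and a short addition to the endpoint definition. No refuser's record is opened. The reported death proportion becomes slightly lower and carries a range.

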### Study endpoints

This phase of the study will have two primary endpoints, namely:The proportion of severe complications (defined as severe pneumonia, acute respiratory distress syndrome, sepsis or septic shock) in patients infected with SARS-CoV-2;The proportion of deaths in patients infected with SARS-CoV-2.

Secondary endpoints will be as follows:The proportion of severe complications according to age group and gender;The proportion of deaths according to age group and gender;

### Sample size calculation

No sample size can be calculated for this phase of the study. Exhaustive inclusion of all cases of COVID-19 followed in the cities of Ouagadougou and Bobo-Dioulasso is planned. At least 1,000 cases are anticipated (as of 28 November 2020, Burkina Faso had a total of 2,886 confirmed cases of COVID-19, of whom 984 were women and 1902 were men). The statistical power of the analyses will be calculated a posteriori*.*

### Data collection and management

Socio-demographic and clinical data (age, gender, comorbidities, vital signs, biological parameters) at the time of diagnosis of COVID-19 will be recorded by the clinical research assistants in the COVID-19 management centers from the patients’ medical files and recorded in the CRF for the study (paper format) (Additional file 2). The development of severe complications (type of complication, date, outcome) will also be recorded in the CRF. In case of death, the date of death will also be recorded. For patients who recover, the end-date for survival analysis will be the date of discharge from the COVID-19 management center.

Data will be recorded in a secure, electronic database using the in-house Ennov software from the Georges-François Leclerc Cancer Centre (Dijon, France). Data will be monitored before locking the database. Data will be analyzed at the Georges-François Leclerc Cancer Centre.

### Statistical analysis

Socio-demographic and clinical characteristics (age, gender, comorbidities, vital signs, biological parameters) of all patients at the time of diagnosis will be described and compared. Quantitative data will be described as mean ± SD or median (range). Qualitative variables will be described as number (percentage). Predictors of the occurrence of severe complications will be identified by logistic regression. The cohort will then be divided into two parts: the first part will be used to generate a score to predict severe complications (development set). The second part of the cohort will be used to validate the predictive score (validation set). The discriminatory capacity of the score will be assessed by the area under the receiver operating characteristic (ROC) curve (AUC), and the sensitivity, specificity, positive and negative predictive values of the score will be calculated. Prognostic factors of survival will be identified for the whole study population using Cox’s proportional hazards regression model. The outcome of interest will be death. Surviving patients will be censored at the date of discharge from the COVID-19 center. Imputation techniques and sensitivity analyses will be performed to account for missing data.

All analyses for phases 1 and 2 will be performed using STATA 14 (Copyright 1985–2015 StataCorp LLC; College Station, TX, USA) and R (www.r-project.org).

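### Phase 2 places predictor selection before the development/validation split, so read in order the score's validation is not independent and its performance is expected to be optimistic

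*Protocol article*

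**What the plan says.** Two places in the protocol article describe how the severity score is built and tested.

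- **Phase 2: Clinical epidemiology (design paragraph).** Data from retrospective files will be used, if there are enough cases, "to construct a score to predict the occurrence of severe complications and death related to COVID-19". Then: "The score will be validated in the prospective cohort to be included after study initiation".
- **Phase 2, Statistical analysis.** The order of steps is: "Predictors of the occurrence of severe complications will be identified by logistic regression. The cohort will then be divided into two parts". The first of these parts serves to build the score. Finally: "The second part of the cohort will be used to validate the predictive score (validation set". Performance is described by AUC, sensitivity, specificity and predictive values. No target AUC, split ratio or split rule is given.

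The Phase 2 sample size section anticipates at least 1,000 cases and gives no event rate or sample size calculation.

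**The concern.** A validation set tests a score only if its outcomes played no part in building it. The analysis section identifies predictors while the cohort is still undivided and splits it afterwards. A variable that is associated with the outcome by chance among the validation patients is then more likely to be selected, and it is later rewarded for that same chance association when the score is tested on those patients. Fitting the coefficients in the development part alone does not undo this.

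At stake is the credibility of the score's stated performance. The Background says that such scores would focus preventive strategies and available resources on high-risk patients, and the design paragraph foresees use in patient management. Once variables have been chosen on all the data, the prospective cohort cannot be made independent again.

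**Working it through.** **1. The two sections side by side**

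| Item | Design paragraph | Statistical analysis |
|---|---|---|
| Data for predictor selection | Not separated from score building, which uses retrospective data | Logistic regression stated before any split, limited to no subset |
| Data for score building | Retrospective cohort | First part of the cohort |
| Validation data | Prospective cohort | Second part of the cohort |
| Outcome of the score | Severe complications and death | Severe complications only |

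The second and third rows can be reconciled if the two parts are the two cohorts, but the text does not say so. The first row is the problem. If prospective patients contribute to selection, they are not independent validation data, however the parts are formed. The fourth row is a smaller mismatch that the same edit can settle.

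**2. Is there a stated figure to reproduce?** No. Phase 2 states no power, event rate or expected AUC. The only input the plan supplies is N = 1,000, its anticipated minimum. Everything else below is an assumption.

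**3. Simulation with some real predictors, and with none.** N = 1,000; 300 replicates per setting; independent candidate predictors; selection by multivariable logistic regression at p < 0.05; model fitted in the development part. Four true predictors had log odds ratio 0.5 per SD. Inflation = mean AUC in the validation part − mean AUC in 20,000 external patients. Differences were taken before rounding, and those below about 0.01 are within simulation error.

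Selection on the whole cohort, then the split:

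| Candidates / true | Development share | 5% events | 10% events | 20% events |
|---|---|---|---|---|
| 15 / 4 | 50% | 0.010 | 0.007 | 0.002 |
| 15 / 4 | 70% | 0.010 | 0.008 | 0.002 |
| 30 / 4 | 50% | 0.042 | 0.008 | 0.005 |
| 30 / 4 | 70% | 0.035 | 0.028 | 0.014 |
| 30 / 0 | 50% | 0.096 | 0.078 | 0.053 |
| 30 / 0 | 70% | 0.104 | 0.074 | 0.059 |

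Example (30 / 0, 50%, 5% events): 0.597 − 0.501 = 0.096.

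With selection in the development part only, the same difference ranged from −0.010 to +0.008 over all 18 settings, that is, zero within simulation error.

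**4. A second simulation, noise predictors only.** N = 1,000; 400 replicates; univariable screening at p < 0.05 on the whole cohort; 50:50 split; true AUC 0.50.

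| Event rate | 20 candidates | 30 candidates | 40 candidates |
|---|---|---|---|
| 5% | 0.565 | 0.585 | 0.604 |
| 10% | 0.550 | 0.559 | 0.578 |
| 15% | 0.538 | 0.556 | 0.565 |

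Inflation therefore runs from 0.538 − 0.50 = 0.038 to 0.604 − 0.50 = 0.104. Selection in the development half gave 0.496 to 0.506.

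**5. Reading the results.** With some true predictors, inflation is about 0 to 0.04. With none, it is about 0.04 to 0.10 over the two simulations. It grows with fewer events and more noise candidates. Within a given split, moving selection into the development part removes it, so the order is the cause. A split at the retrospective/prospective boundary would be affected in the same way.

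**The case against.** **The two sections may agree on the split.** The design paragraph lists the retrospective cohort first and the prospective one second, and the analysis section develops on a first part and validates on a second. A reader might infer that the sections define different validation sets, or that a random split of pooled data replaces the out-of-time test. The documents do not support that: no random split, ratio or pooling is mentioned. This objection stands. The fair statement is that the link between the sections is not made.

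**Selection on the whole cohort is inferred.** The analysis section speaks explicitly of all patients only for the survival model: "Prognostic factors of survival will be identified for the whole study population". Identifying predictors of severe complications is also an objective in its own right in the Background, and all patients are suitable for that. The logistic regression sentence could describe that separate analysis. This softens the point but does not remove it, because the section gives no other selection step for the score and places this one before the division.

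**The size may be small.** A reader might infer from the noise-only results that the reported AUC will be inflated by up to 0.10. That is the extreme case. The candidates named (age, gender, comorbidities, vital signs, biological parameters) are unlikely to be all noise, and with 15 candidates, four of them real, inflation could not be told from zero. This stands, and it limits the claim to expected optimism of unknown size.

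**The score is conditional, and an article condenses.** The Phase 2 primary endpoints are proportions of complications and deaths, which are unaffected, and the score is built only if numbers allow. Selection details may well be left to a fuller document. But a stated sequence is not an omission, and as stated it does not protect the validation set.

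**Conclusion.** The point holds in a limited form. Followed in the order written, the analysis section lets validation outcomes influence the choice of variables, so the validation performance is expected to be optimistic and the prospective cohort loses the independence that the design paragraph gives it. The direction is known. The size is not, because it depends on the event rate and the number of candidate predictors, which the protocol does not state. Under the assumptions shown, it was about 0 to 0.04 on the AUC scale with some true predictors and about 0.04 to 0.10 with none. The conclusion rests on two readings: that the word order means selection precedes the split, and that the selected predictors feed the score. It does not rest on the split being random, and the two sections are unreconciled rather than in plain contradiction.

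**What to change.** Reword the Phase 2 Statistical analysis section so that:

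- the development and validation sets are explicitly the retrospective and prospective cohorts of the design paragraph;
- all predictor selection and model fitting for the score use the development cohort only;
- the frozen score is then applied to the prospective cohort;
- a regression on the whole cohort, if wanted for the objective on predictors, is reported as a separate descriptive analysis that does not feed the score;
- the outcome of the score is the same in both sections.

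The design paragraph makes the score depend on case numbers, so state the fallback too: with too few cases, develop on all data and correct optimism by bootstrap, repeating the selection step in every resample.

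The cost is wording, plus a lower reported AUC. The drop is slight when events are plentiful: in the 15-candidate, four-true setting with 20% events and a 50:50 split, the validation AUC went from 0.740 to 0.733. It is larger when events are scarce: with 30 candidates, four true, and 5% events it went from 0.747 to 0.666. Part of that drop is real, since selecting on half the patients lowered the external AUC from 0.705 to 0.662. That is a reason to prefer the bootstrap route when events are few.

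### The phase 2 severity score is built and tested without setting apart patients already severe at diagnosis, so its reported accuracy would probably overstate prediction of later complications

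*Protocol article*

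**What the plan says.** All references are to Phase 2 of the protocol article unless stated.

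- **Population.** Inclusion criteria: "All patients followed for COVID-19 (whether they are or were hospitalized or not". The only non-inclusion criterion is "Patients who refuse the use of their medical records for research purposes". Neither mentions severity at diagnosis.
- **Outcome.** Study endpoints: "The proportion of severe complications (defined as severe pneumonia, acute respiratory distress syndrome, sepsis or septic shock". No onset time is attached.
- **Timing of clinical data.** Data collection and management: "Socio-demographic and clinical data (age, gender, comorbidities, vital signs, biological parameters) at the time of diagnosis of COVID-19".
- **Dates.** The same section states: "The development of severe complications (type of complication, date, outcome) will also be recorded in the CRF".
- **Model.** Statistical analysis: "Predictors of the occurrence of severe complications will be identified by logistic regression". The cohort is then divided into a development and a validation set.
- **Performance.** "The discriminatory capacity of the score will be assessed by the area under the receiver operating characteristic (ROC) curve (AUC"; sensitivity, specificity and both predictive values are also to be calculated.

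The opening text of Phase 2 assigns development to the retrospective patients and validation to the prospective ones. It gives the purpose of the score as predicting severe complications and death so that management can be optimised.

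**The concern.** A prediction score needs people who do not yet have the outcome when the predictors are measured. The plan sets no such condition. A patient diagnosed while already in severe pneumonia or septic shock is an event, and measurements taken during that illness are available as its predictors. The date of each complication is collected, but no stated rule uses it to decide who is at risk.

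Such patients should be expected. The Background says that management in Burkina Faso has centred on people who present with severe disease, and the four named sites are the main treatment centres for the two cities.

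At stake is the use of the score. It is meant to direct scarce resources to patients likely to deteriorate. If part of its apparent accuracy comes from recognising patients who have already deteriorated, the published figures will not carry over to those not yet severe. An overall validation figure would not show this, because the validation patients enter under the same rule.

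**Working it through.** **No figure to reproduce.** Phase 2 states no event rate, AUC or sample size. The one sum available, 984 women + 1,902 men = 2,886 confirmed cases, agrees with the stated total.

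**Step 1: direction.** Let *f* be the share of events already present at diagnosis. For a fixed score and one common group of non-events, the pooled AUC is the event-weighted mean:

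AUC(all) = *f* × AUC(present) + (1 − *f*) × AUC(later)

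It exceeds AUC(later) whenever events already present are easier to separate from non-events than later ones are. That is plausible, since the measurements are taken while the complication is under way.

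At a fixed cut-off:
- Sensitivity is the same kind of weighted mean.
- Positive predictive value rises: true positives are added and false positives are unchanged.
- Specificity does not change.
- Negative predictive value does not rise, because any missed cases already present add to the false negatives.

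The overstatement therefore concerns AUC, sensitivity and positive predictive value.

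**Step 2: illustrative size.** Every input is an assumption, not a figure from the document. AUC(later) = 0.70.

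| *f* | AUC(present) 0.90 | 0.95 | 0.98 |
|---|---|---|---|
| 0.25 | 0.750 | 0.762 | 0.770 |
| 0.50 | 0.800 | 0.825 | 0.840 |
| 0.75 | 0.850 | 0.887 | 0.910 |

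For example, 0.50 × 0.90 + 0.50 × 0.70 = 0.800.

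**Step 3: simulation with the model refitted.** Assumptions: 200,000 patients; severe complications in 15% or 30%; one background factor shifted 0.6 SD in all severe cases; one diagnosis-time vital sign shifted 0.5 SD in later-onset cases and 1.5 or 2.5 SD in cases already severe.

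| Share already severe | AUC, everyone included | AUC, restricted to those not yet severe and refitted |
|---|---|---|
| 0% | 0.71 | 0.71 |
| 25% | 0.75–0.77 | 0.71 |
| 50% | 0.78–0.83 | 0.71 |
| 75% | 0.83–0.89 | 0.71 |

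With 25% to 75% already severe, the all-patient model, when assessed only in patients not yet severe, reaches an AUC of 0.68 to 0.71. Its vital-sign coefficient is 0.7 to 1.6, against about 0.5 in the restricted model. In these scenarios the ranking of patients not yet severe suffers little. The larger damage is to the reported performance and to the weight given to the vital sign.

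**The case against.** The strongest reply is that this is silence rather than error. An article condenses a fuller protocol, and the at-risk set may be defined there. The wording leans towards new onset: the text speaks of complications occurring and developing, places the clinical data at diagnosis and records a date for each complication. The logistic sentence also lacks the whole-population phrase that the Cox sentence carries.

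This shows intent, and it stands as such. But the article does fix the population, the outcome, the timing of the data, the split and the performance measures. Followed as written, they mix the two kinds of event, and no rule carries the intent out.

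Some stronger readings are tempting but not supported:

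- *That the vital signs define the outcome, making the score circular.* No criteria are given for the four complications, and the candidate predictors are not formally listed. That diagnosis-time measurements are candidates is the evident reading. That they define the outcome is a clinical inference.
- *That the AUC will be inflated by a known amount.* No share already severe is given. The Background remark describes how the epidemic was managed, not the make-up of this cohort, and outpatients are included.
- *That the score is fitted on every patient at once.* It is built in a development set. The point is only that neither set is restricted by severity at diagnosis.
- *That validation could never reveal the problem.* It could if results were split by onset date, but no such split is planned.

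One practical objection also stands: onset dates taken from retrospective files may be missing or imprecise.

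**Conclusion.** The concern holds in a limited form. As written, complications already present at diagnosis are pooled with those to be predicted. The resulting AUC, sensitivity and positive predictive value would probably overstate performance for later complications. The direction rests on two premises: that some patients are already severe at diagnosis, which the Background makes likely, and that these patients are easier to distinguish using diagnosis-time data.

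The size cannot be established. Under the assumptions shown, an AUC near 0.70 could read anywhere from 0.75 to 0.91 when 25% to 75% of events are already present. With none present there is no bias. The primary endpoint proportions are unaffected. The change should be made because it is specific, inexpensive and fits the stated purpose better than the analysis described.

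**What to change.** Amend Phase 2, Statistical analysis, to say that:

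1. The severe-complication score is developed and validated in patients free of all four listed complications at diagnosis, and only complications dated after diagnosis count as events.
2. Patients already severe at diagnosis are described separately and stay in the primary endpoint proportions.
3. The model in all patients is reported as a sensitivity analysis.
4. A stated rule classifies patients whose onset date is missing or falls on the day of diagnosis.

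The case report form already collects complication dates, so no new data item is needed. The price is fewer events for a score whose construction already depends on the number of cases collected, a probably lower AUC, and dependence on onset dates that may be incomplete in the retrospective files. The rule in item 4 therefore needs care, and results under alternative classifications of doubtful dates would show how much it matters.
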